#### Improvement in clinical and social functioning during hospital admission

Although we expect variation in how frequently HoNOS scores are collected and some missing data, we will attempt to extract HoNOS scores at two time points of a patient’s psychiatric admission: the closest HoNOS score recorded around the admission date (± a maximum of 3 months) and the closest recorded HoNOS score to the discharge date (± a maximum of 3 months). A linear regression model will be carried out with the difference in total HoNOS score as the dependent variable. C(E)TR group will be the main independent variable of interest, with baseline HoNOS included as a covariate. Age, sex and ethnicity will be included as confounders. We want to understand if having a community C(E)TR before hospital admission is associated with greater improvements while in hospital. As variations of HoNOS are applied across different populations, we will carry out this analysis on the version that has the least missing data.

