### Outcomes

Outcome measures are the length of hospital stay (number of days), and clinical and functional improvement while in hospital. The Health of the Nation Outcome Scales (HoNOS) is a clinician-rated clinical and social functioning assessment scale with 12 items, each rated between 0 (no problem) and 4 (very severe problem).^16^ It has good psychometric properties.^17 18^ The HoNOS is routinely recorded by NHS staff at intervals and at points of care transition (eg, hospital admission and discharge).

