### Inclusion and exclusion criteria

All eligible patients who were admitted to a psychiatric hospital for at least 14 days may be included in this study. We will exclude people who were not open to a SLaM community team for at least 6 months prior to their admission, as these people may have a high degree of missing data and may not have had an opportunity for a community C(E)TR before their admission or might represent new transfers from other NHS Trusts. We will also exclude ‘re-admissions’, defined as an admission occurring <6 months after the discharge date of a previous admission.

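### The ±3-month HoNOS windows around admission and discharge overlap for stays under about 6 months, so one rating can serve as both scores and record a false zero change

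*Protocol article*

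**What the plan says.** The subsection of the Protocol article on improvement in clinical and social functioning during admission defines two scores per stay. The admission score is "the closest HoNOS score recorded around the admission date (± a maximum of 3 months"). The discharge score is "the closest recorded HoNOS score to the discharge date (± a maximum of 3 months"). The model follows: "A linear regression model will be carried out with the difference in total HoNOS score as the dependent variable", with C(E)TR group as the exposure and baseline HoNOS, age, sex and ethnicity as covariates.

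Eligibility for Sub-study 2 (Inclusion and exclusion criteria) covers patients "admitted to a psychiatric hospital for at least 14 days".

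Two other statements bear on the point. The Outcomes section says: "The HoNOS is routinely recorded by NHS staff at intervals and at points of care transition (eg, hospital admission and discharge"). The HoNOS subsection itself concedes that "we expect variation in how frequently HoNOS scores are collected and some missing data".

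The article does not say that the two scores must come from different ratings, that they must be in date order, or that the discharge score must be later than the admission date.

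**The concern.** The analysis is meant to show whether patients with a prior community C(E)TR improve more while in hospital. That needs a rating that describes the patient at the start of the stay and another that describes the patient at the end. Two windows of 3 months either side of their dates cannot be kept apart when the dates themselves are only weeks apart.

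If one rating is the closest to both dates, the computed change is exactly 0 whatever happened to the patient. This is a missing score entered as a measured absence of change. It pulls the mean change towards zero, and adjusting for baseline HoNOS does not repair it.

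The defect also depends on length of stay, which Table 1 gives as the primary outcome of Sub-study 2. If C(E)TRs shorten stays, as intended, the two groups could carry different shares of false zeros.

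**Working it through.** **Inputs.** Half-window W = 3 months, taken as 91 days (HoNOS subsection). Minimum stay 14 days (Inclusion and exclusion criteria). The article gives no HoNOS recording rate and no distribution of length of stay, and it states no figure on this point that could be reproduced.

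**Step 1: overlap.** Count days from admission and let the stay last L days. The admission window runs from −W to W and the discharge window from L − W to L + W. They share the days from L − W to W, so the overlap is 2W − L = 182 − L days, and it vanishes at L = 182.

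| Stay L (days) | Overlap 182 − L (days) | Share of each 182-day window |
|---|---|---|
| 14 | 168 | 92% |
| 28 | 154 | 85% |
| 60 | 122 | 67% |
| 90 | 92 | 51% |
| 120 | 62 | 34% |
| 150 | 32 | 18% |
| 182 | 0 | 0% |

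**Step 2: where the overlap lies.** At L = 14 it runs from day 14 − 91 = −77 to day 91. That is 77 days before admission and 91 − 14 = 77 days after discharge. A single rating from either period would qualify as both scores, so an admission score can postdate discharge and a discharge score can predate admission.

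**Step 3: what the closest-rating rule does.**

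- One rating in the overlap: it fills both slots and the change is 0.
- Two ratings can give the same result. Take L = 14 with ratings on days −40 and 5. Distances to admission are 40 and 5; distances to discharge are 54 and 9. The day-5 rating wins both times.
- Separate ratings close to each date: the rule picks different ones and the change is valid.
- The rule never picks a later rating for admission than for discharge. For that, admission would have to lie at or after the midpoint between the two ratings and discharge at or before it, although admission comes first. An admission score after discharge, or a discharge score before admission, is therefore always a shared rating. Date order becomes a live issue once distinct ratings are demanded, because the next-closest rating could then be on the wrong side.

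**Step 4: dependence on length of stay.** Take a patient whose only rating is on the admission date. If L is at most 91 days, that rating lies in the discharge window and the change is 0. If L exceeds 91 days, the discharge score is missing. The same record is scored differently according to the length of stay.

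**Step 5: illustrative size.** Assume that each transition rating is recorded independently with probability q, that there are no other ratings, and that the stay is under about 3 months. Among patients with any score, the share with one rating used twice is 2q(1 − q) / [1 − (1 − q)²].

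- q = 0.9: 0.18 / 0.99 = 18%
- q = 0.7: 0.42 / 0.91 = 46%
- q = 0.5: 0.50 / 0.75 = 67%

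If true change is unrelated to which ratings were recorded, the mean change shrinks to 82%, 54% and 33% of its true value. Simulation with extra ratings at random times, one per 3 months on average, lowers the shares. For q = 0.9 they are about 14%, 10% and 5% at stays of 14, 30 and 60 days; for q = 0.7, about 38%, 27% and 14%. All values of q are assumptions.

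**The case against.** The best defence is that HoNOS is routinely recorded at admission and discharge, the two anchor dates. Where both ratings exist, the closest-rating rule picks the right pair and the overlap does no harm. The subsection also speaks of two time points, which signals that a pair is intended, and tie-breaking rules are often left to a fuller document. HoNOS change is secondary in Table 1 (though the abstract lists clinical change among the primary outcomes), and the question is put as one of association.

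The first argument limits the size but does not remove the problem, since the article itself expects irregular recording and gaps. The second carries less weight, because the windows, the selection rule and the outcome variable are all stated. Followed as written, they yield a wrong value where a missing one belongs. The third bears on severity only.

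Three stronger readings are tempting and are not supported:

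- A reader might take the 92% overlap as the rate of false zeros, or assume ratings at random times, which at one every 2 to 3 months would give about 77% to 85% for 14-day stays. Overlap measures window geometry, and random timing ignores the stated recording at transitions.
- A reader might infer that the C(E)TR group must appear to improve less. Nothing in the article shows that length of stay or recording differs between groups.
- A reader might fault the rule that "we will carry out this analysis on the version that has the least missing data". It is a trade-off: it is fixed in advance, selects on completeness and not on the C(E)TR effect, and avoids mixing totals from different variants, at the price of a narrower population.

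**Conclusion.** The point holds as a should-fix. The geometry is exact: the windows overlap for every eligible stay under about 6 months, by 168 of 182 days at the minimum stay, and the stated rule lets one rating act as both scores. The result is a false zero that masks a missing score.

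The frequency cannot be derived from the article. It could be small if transition ratings are nearly complete. Under the transitions-only assumption for stays below about 3 months, it is about 18% of scored patients at 90% recording and 46% at 70%. Where false zeros are equally common in both groups, they pull the group difference towards zero. They could distort it in either direction if their share differs between groups, which is possible because the share depends on length of stay but is not shown.

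**What to change.** Change the extraction rule in the HoNOS subsection:

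1. Require two distinct ratings, the discharge score dated later than the admission score.
2. Let no rating be eligible for both slots. One way is to split the stay at its midpoint: the admission score is the closest rating before the midpoint, the discharge score the closest after it, each still within 3 months of its date. A rating on the midpoint itself is assigned to one side by a fixed rule. Stays of 6 months or more are essentially unaffected.
3. Treat a patient with only one rating as having missing change, not zero.
4. Report, by C(E)TR group, how many patients have two ratings, one or none, and how many would have had one rating used twice under the present rule.

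No new data are needed. The cost is that some pairs now scored as zero become missing, so the analysed sample shrinks and the missingness has to be handled openly. Part of this is recovered: in the two-rating example above (14-day stay, ratings on days −40 and 5), the midpoint is day 7, both ratings fall before it, and change is correctly missing. Had the later rating been on day 10, the present rule would still use it twice (10 against 40 days from admission, 4 against 54 from discharge), whereas the split yields a valid pair.

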### Matching a control group

We will match between one and five controls, who will not have a community C(E)TR, per patient who has a C(E)TR. Eligibility will be a diagnosis of intellectual disability or autism and having received a continuous period of community care within SLaM services for at least a year between 1 January 2015 and 31 December 2023. Matching will be based on age (±3 years), sex (male/female) and diagnosis (intellectual disability with/without autism, or autism without intellectual disability). Controls should be under an active episode of community care and not be an inpatient on the index date of their matched case. They must also have been under SLaM services for a similar total duration of their matched case (±2 years). Matching with replacement will be applied to ensure every case has an appropriate match according to these criteria. A pseudo-index date for each control will be assigned and will be the same as the index date of their matched case.

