##### Stage 1: propensity scores

As the retrospective analysis of EHRs is not a randomised controlled study, we will employ a propensity score weighting technique to adjust for confounders in the data. Propensity scores will balance the C(E)TR and comparison groups on a set of baseline (pre-index date) characteristics.^12^ Certain characteristics may increase the probability of someone receiving a C(E)TR, and we wish to account for these in the outcome (risk of hospitalisation) model. Scores will be calculated by fitting a multivariable logistic regression model with C(E)TR status as the dependent variable.^13^ We will condition on baseline characteristics that are believed to be related to the outcome, risk of hospitalisation, and to the probability of receiving a C(E)TR (confounders), but not those that might lie on the causal pathway from receiving a C(E)TR to being admitted to hospital (mediators), that is, variables that are affected by the intervention itself. The following variables are expected to be included in the propensity score analysis: age, sex, ethnicity, marital status, sexual orientation, deprivation score, relevant diagnosis (intellectual disability with/without autism, or autism without intellectual disability) and pre-existing psychiatric diagnoses (online supplemental table 1).

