### Identifying cases and controls

Using the review of clinical records of eligible patients previously described, we will measure whether each patient had a community C(E)TR within 6 months prior to their psychiatric hospital admission. We will form two groups: those who had a pre-admission community C(E)TR, and those who did not.

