#### Time-to-event analysis

Time-to-discharge (length of hospital admission) will be analysed using the Kaplan-Meier estimator.^19^ A Cox’s proportional hazards model will be used to estimate the HR for discharge,^20^ comparing those who received a C(E)TR to those who did not receive a C(E)TR for a follow-up period of 6 months after admission. This analysis will be adjusted for C(E)TR status prior to admission, age at admission, sex, ethnicity and relevant diagnosis at admission (intellectual disability with/without autism, or autism alone). Patients who die within 6 months of admission will be censored at the date of death, and patients who remain in hospital will be censored at the end of the 6 months.

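### The HoNOS-change regression omits the diagnosis group that the Cox model adjusts for in the same unmatched hospital cohort, which leaves a possible and avoidable source of confounding

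*Protocol article*

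**What the plan says.** The section on improvement in clinical and social functioning sets out the model completely. On the outcome: "A linear regression model will be carried out with the difference in total HoNOS score as the dependent variable". On the exposure and baseline: "C(E)TR group will be the main independent variable of interest, with baseline HoNOS included as a covariate". On the rest: "Age, sex and ethnicity will be included as confounders". Diagnosis is not listed, and no reason is given. The section also restricts the analysis to whichever HoNOS version has the least missing data, because versions differ by population.

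The section just before it, Time-to-event analysis, adjusts the Cox model for C(E)TR status and for "age at admission, sex, ethnicity and relevant diagnosis at admission (intellectual disability with/without autism, or autism alone").

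Sub-study 1 uses the same diagnosis factor twice. Under Matching a control group: "Matching will be based on age (±3 years), sex (male/female) and diagnosis". Under Stage 1: propensity scores, the expected variables include "relevant diagnosis (intellectual disability with/without autism, or autism without intellectual disability) and pre-existing psychiatric diagnoses", on the ground that "Certain characteristics may increase the probability of someone receiving a C(E)TR, and we wish to account for these in the outcome" model.

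Sub-study 2 has neither matching nor weighting. Under Identifying cases and controls: "We will form two groups: those who had a pre-admission community C(E)TR, and those who did not".

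**The concern.** In an unmatched, unweighted comparison, the regression covariates are the only adjustment. The plan regards diagnosis as related to who receives a C(E)TR, and it adjusts for diagnosis when it analyses length of stay in this cohort. The HoNOS model drops it. Apart from baseline HoNOS, which only the HoNOS model needs, diagnosis is the one difference between the two covariate lists.

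Baseline HoNOS does not replace it. Two people with the same admission total can still be expected to change by different amounts if change depends on diagnosis. If the C(E)TR group also has a different share of people with intellectual disability, part of that difference is credited to the C(E)TR. The affected result is the plan's only measure of clinical improvement in hospital. The abstract names it among the primary outcomes, and Table 1 lists it as secondary.

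**Working it through.** The article gives no sample size, HoNOS standard deviation, diagnostic mix by group or expected effect for this analysis, so there is no planned figure to reproduce. The check compares the covariate lists and then illustrates size on stated assumptions.

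**Step 1: where diagnosis is handled**

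| Analysis | Matched or weighted | Diagnosis adjusted for |
|---|---|---|
| Sub-study 1, admission | Matched, propensity-weighted | Yes, in both |
| Sub-study 2, length of stay (Cox) | No | Yes |
| Sub-study 2, HoNOS change | No | No |

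The Cox model takes diagnosis at admission, so the variable is available for this cohort.

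**Step 2: formula.** With diagnosis omitted, the bias in the C(E)TR coefficient is

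bias = γ × δ

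- γ: difference in HoNOS change between the two diagnosis groups, given baseline HoNOS, age, sex and ethnicity.
- δ: difference between the C(E)TR groups in the share with intellectual disability, after adjustment for the same covariates. If those covariates explain part of a raw imbalance, δ is smaller than the raw difference in shares.

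If either is zero, there is no bias.

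**Step 3: illustration (both inputs assumed)**

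- δ = 0.10, γ = 1: 0.10 × 1 = 0.1 points
- δ = 0.30, γ = 2: 0.30 × 2 = 0.6 points
- δ = 0.30, γ = 3: 0.30 × 3 = 0.9 points

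The protocol describes 12 items scored 0 to 4, so the total runs to 12 × 4 = 48. The range is then 0.1/48 = 0.2% to 0.9/48 = 1.9% of the scale.

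**Step 4: simulation.** All inputs are assumed: no true C(E)TR effect, 50 against 200 patients, residual SD 5.2, 2,000 runs per scenario, and age, sex and ethnicity unrelated to diagnosis, so that δ stays close to the raw difference.

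| Share with intellectual disability | γ | Bias, planned model | False positives at 5%, planned model |
|---|---|---|---|
| 50% v 50% | 1, 2, 3 | 0.03, 0.00, 0.02 | 5.5%, 4.4%, 5.0% |
| 60% v 40% | 1, 2, 3 | 0.18, 0.40, 0.62 | 6.0%, 8.0%, 11.7% |
| 70% v 40% | 1, 2, 3 | 0.30, 0.61, 0.87 | 7.2%, 11.4%, 17.8% |

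With diagnosis added, the mean estimate lay between -0.04 and 0.04 and the false-positive rate between 4.3% and 5.5% in every scenario.

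Hand check of the 70% v 40%, γ = 2 cell: SE = 5.2 × √(1/50 + 1/200) = 0.82; 0.6/0.82 = 0.73; Φ(0.73 − 1.96) + Φ(−0.73 − 1.96) = 0.109 + 0.004 = 11.3%, against 11.4% simulated.

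The false-positive rates depend on the assumed sample size and SD. The bias depends only on γ and δ.

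**The case against.** The strongest answer is the single-version restriction. The plan itself links HoNOS versions to populations, so analysing one version may narrow the diagnostic mix. If that version covered essentially one diagnosis group, the factor would hardly vary and the problem would largely vanish. This stands as a limit on the point. It does not remove it, because the version is chosen by completeness, not by diagnosis, and nothing says that the version chosen will be confined to one group. A reader might infer that nothing at all restrains diagnostic imbalance in this analysis; that goes too far.

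The section also asks only about association; explicit causal modelling belongs to sub-study 1. That makes the claim more modest, but the plan calls these covariates confounders, so confounding is its own concern here.

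One could say that covariates are a matter for the analysis plan. This list, however, is fixed in the article, without the wording used for the propensity model that variables are only expected to be included.

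A reader might also infer that pre-existing psychiatric diagnoses and deprivation belong in this model because the propensity model has them. The comparison with the Cox model does not support that. The Cox model has neither, they were chosen for a different outcome (admission), and they could use more degrees of freedom and bring more missing data. The baseline tables split by diagnosis would show an imbalance but would not adjust for it.

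**Conclusion.** The omission is real and inconsistent with the neighbouring model for the same cohort. Whether it biases the result depends on two conditions that the documents leave open: a diagnostic imbalance remaining after the listed covariates, and a difference in HoNOS change by diagnosis at a given baseline. Neither size nor direction can be stated. The 0.1 to 0.9 points rests wholly on assumed inputs and, for a given imbalance in raw shares, would be smaller if the other covariates explain part of it.

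Two stronger readings are not supported. A reader might infer that length of stay and HoNOS change could conflict merely because their adjustment sets differ. But one is a hazard ratio for discharge and the other a mean change in a clinician rating, and nothing in the plan says they should agree. A reader might also infer a loss of power, but the plan states no power or sample size from which to measure one. The case for the change is possible confounding, removable at little cost.

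**What to change.** In the section on improvement in clinical and social functioning, add relevant diagnosis at admission, as the same two-level factor used in the Cox model, to the covariates of the HoNOS-change regression. If the HoNOS version chosen turns out to cover essentially one diagnosis group, leave the factor out and say so, with the diagnostic make-up of the analysed sample.

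No new extraction is needed. The cost is one degree of freedom, which matters only if few admissions have both an admission and a discharge HoNOS score.

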### Missing data

The design of the study ensures that the intervention and outcome are fully observed; however, owing to the nature of the data source, we anticipate non-trivial proportions of missing confounder data. We will report the proportion and frequency of missing values for covariates. We will consider the missingness pattern approach, a technique which, if key assumptions are not violated, retains all people in the analysis. We will undertake various sensitivity analyses to explore whether our conclusions are affected when the assumption for the missing pattern approach is violated.^21^ A similar approach will be applied to the economic analysis, where missing data will be addressed using multiple imputation by chained equations with predictive mean matching.^22^

### Extensions of sub-study 1 and sub-study 2

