### Study eligibility criteria

Individuals of any age with a diagnosis of intellectual disability (ICD-10 code F7x) or autism (ICD-10 code F84) will be identified using diagnostic information entered into structured fields or in the free text record using the NLP diagnosis application. Participants must have a recorded diagnosis of intellectual disability and/or autism. Eligible participants must have received an episode of care from a community mental health service provided by SLaM for at least one continuous year between 1 January 2015 and 31 December 2023 to ensure that sufficient data are held in the record. All eligible episodes of care will be included, including those individuals with more than one period of community care of at least 1 year during this timeframe.

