### Index date

The index date will be defined as the date on which a community C(E)TR was held.

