### Outcome

The primary outcome will be psychiatric hospital admission (treated as a binary variable) at any time within 6 months after the index date (online supplemental table 2).

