#### Economic analysis

A partial economic evaluation will assess the cost impact of community C(E)TRs on secondary healthcare use. The primary outcome will be total secondary healthcare cost per patient, comparing those who received a community C(E)TR with those who did not. Service use data will be derived from CRIS and HES. Database accessibility and relevant resource use variables will be reviewed to determine feasibility. If both CRIS and HES are used, discrepancies for the same patient will be checked manually. Due to the linkage, the end date for the HES data extraction will be 31 March 2024. For HES data, the HRG Grouper and Spell Converter will be used to classify activity and define spells of care. Unit costs will be based on NHS Reference Costs and costs published by the Personal Social Services Research Unit (PSSRU).^23^ Mean cost differences and 95% CI will be estimated using non-parametric bootstrap regression (5000 replications), adjusting for baseline costs and covariates from the main analysis. Service-specific utilisation will be summarised descriptively without formal comparisons, to focus on total cost and avoid multiple testing issues.

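### The plan says the outcome is fully observed by design, but sub-study 1 has no rule that secures the 6 months before and after the index date

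*Protocol article*

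**What the plan says.** All references are to the protocol article.

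- **Missing data:** "The design of the study ensures that the intervention and outcome are fully observed". The section then plans for missing confounders, and for missing data in the economic analysis.
- **Study eligibility criteria:** participants need community care "for at least one continuous year between 1 January 2015 and 31 December 2023". The year may fall anywhere in that period.
- **Index date (sub-study 1):** "The index date will be defined as the date on which a community C(E)TR was held". No position within the care episode and no calendar limit is given.
- **Outcome (sub-study 1):** "psychiatric hospital admission (treated as a binary variable) at any time within 6 months after the index date".
- **Matching a control group:** controls must be in active community care and not an inpatient on the case's index date, with total time under the Trust (SLaM) within two years of the case's.
- **Causal effect section and Stage 2:** the difference-in-differences (DiD) model compares change from the 6 months before index to the 6 months after.
- **Sub-study 2, Inclusion and exclusion criteria:** "We will exclude people who were not open to a SLaM community team for at least 6 months prior to their admission". The reasons given include missing data and new transfers from other Trusts. The time-to-event section censors at death.
- **Economic analysis:** "the end date for the HES data extraction will be 31 March 2024". Other extraction runs to 31 December 2024 (Study setting).

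**The concern.** A DiD estimate on a yes/no admission variable needs both windows to be seen for each person. If someone transferred in shortly before the index date, an earlier admission elsewhere may not be in the record. If someone dies or moves away shortly after it, the remaining follow-up cannot contribute a recorded admission. HES is described as covering general hospital care, so the article names no source for psychiatric admissions outside the Trust.

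The authors recognise this problem in sub-study 2 and guard against it there. Sub-study 1 uses the same records, treats the pre-index window as an outcome period, and carries the study's only causal claim, but it has neither safeguard. The 12-month extension doubles the windows without adding a rule. The statement in the Missing data section tells readers that the problem cannot arise.

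**Working it through.** The article gives no admission rate, event count or loss figure, so there is no figure of its own to reproduce. Four checks follow.

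**1. Do the stated rules secure the windows?**

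| Needed | Sub-study 1 | Sub-study 2 |
|---|---|---|
| 6 months seen before index | No rule; one year of care at any time | At least 6 months open to a community team |
| 6 months seen after index | No rule | Follow-up to 6 months, with censoring |
| Death | No rule | Censored at death |
| Controls or comparators | In active care on the index date | Same look-back rule as the exposed |

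A review held in the second week of a year-long episode qualifies, and so does one held in its eleventh month. The Missing data statement also sits badly with sub-study 2's own section on clinical improvement, which expects missing scores on the Health of the Nation Outcome Scales, an outcome measure.

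**2. Calendar coverage (dates from the article).**
- Clinical record: from 31 December 2023 to 31 December 2024 is 366 days. Index dates up to the end of 2023 therefore have 6 and 12 months of calendar follow-up.
- HES: 6 months before 31 March 2024 is 30 September 2023, and 12 months before is 31 March 2023.
- 1 January 2015 to 31 December 2023 is 3,287 days. With index dates assumed uniform, those after 30 September 2023 are 92/3,287 = 2.8%, and those after 31 March 2023 are 275/3,287 = 8.4%. These lack full 6-month and 12-month HES costs respectively.

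**3. What unobserved time could do (all rates assumed).** Let p be the true admission risk, equal in both groups and both periods, with no effect of the review. Let uT and uC be the shares of the review and control groups whose post-index window is unseen and reads as no admission.
- Observed post-index risks are p(1 − uT) and p(1 − uC), so spurious DiD = p(uC − uT).
- uT = 0, uC = 10%: +1.0, +2.0 and +3.0 points at p = 10%, 20% and 30%. Reversing the loss gives −1.0, −2.0 and −3.0.
- uT = uC: zero. With a true effect, equal loss only shrinks it: 20% against 30% with 10% loss in each group reads −10 × 0.9 = −9.0 points.
- True effect of −5 points (25% against 30%): with uT = 0, uC = 10% it reads 25.0 − 27.0 = −2.0; with uT = 10%, uC = 0 it reads 22.5 − 30.0 = −7.5.
- For unseen look-back shares vT and vC, the same algebra gives p(vT − vC): equal in size, opposite in sign.

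**4. What a look-back rule could cost.** If observation meant lying inside one community episode of L months, with a uniform index date, a 6-month look-back keeps (L − 6)/L of events: 50% at L = 12 and 75% at L = 24. Requiring 6 months on both sides keeps (L − 12)/L: 0% at 12 months, 33% at 18, 50% at 24, 67% at 36 and 80% at 60. These are lower bounds on what is kept, because a person can be under the Trust's services, with admissions recorded, outside that episode.

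**The case against.** **Coding is inferred.** A reader might conclude that people who die or leave are coded as not admitted. The article does not say so. It follows naturally from a yes/no variable built on recorded spells with no censoring rule, but the outcome definition points to a supplement and the model assumptions to an appendix, neither of which is shown. This stands, so the coding should not be asserted as fact.

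**Outside an episode is not unobserved.** All psychiatric inpatient spells are extracted for the cohort and the electronic record dates from 2006. A Trust admission before or after a community episode can still be recorded. This stands, and it narrows the gap to recent transfers in, death, moving away and admission outside the Trust.

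**Controls share the weakness.** They fall under the same one-year rule and take the case's index date. A reader might infer a spurious rise in the review group from missing look-back among cases alone; that assumes controls lose nothing, and nothing in the article shows that review recipients are more often newly referred. This stands: neither direction nor size can be claimed.

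**Wording and dates.** Total duration under services may mean duration up to index, so the matching rule is ambiguous rather than wrong. Index dates in 2024 would also strain the stated care window, so shortfalls computed on them are not relied on.

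**HES is secondary.** It affects a cost extension, its use is subject to feasibility, imputation is planned for missing economic data, and matched controls are truncated at the same date. This lowers its weight, but the truncation remains.

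**Sub-study 2's rule has other reasons too,** including the opportunity to have a review before admission. That is true, but missing data and transfers are also named there and apply equally to sub-study 1.

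None of this makes the Missing data statement correct.

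**Conclusion.** The point holds as a wrong affirmative statement about sub-study 1's primary outcome. The stated rules do not secure either 6-month window, although sub-study 2 shows that the authors know how to do so. It goes beyond detail left to a fuller document, because the article asserts the opposite.

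The likely bias cannot be sized or signed. Unobserved time creates an effect where none exists only if it differs by group, given equal underlying risks. The illustration of 1 to 3 points, in either direction, rests on an assumed 10-point difference in unobserved follow-up, an assumed risk of 10% to 30%, and unseen windows reading as no admission. The HES shares of 2.8% and 8.4% rest on uniform index dates over 2015-2023 and on cost windows of 6 and 12 months. Calendar follow-up in the clinical record is adequate for index dates to the end of 2023; the gap there is at the level of the person.

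**What to change.** 1. Require cases and controls to have been under SLaM services for at least 6 months before the index date, and 12 months for the 12-month horizon. If this loses many events, make it at least a sensitivity analysis.
2. Match on duration of care up to the index date, and say so.
3. State how death and known departure after index are handled, by censoring or by weighting for censoring, and report observed time before and after index by group.
4. State that sub-study 1 index dates end on 31 December 2023.
5. Limit HES-based costs to index dates up to 30 September 2023 for 6 months and 31 March 2023 for 12 months.
6. Replace the sentence in Missing data with one that says what is observed, for whom, and which psychiatric admissions outside the Trust cannot be seen.

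The work is eligibility wording, date filters and one handling rule. The real cost is lost events: few at the HES limits, but possibly a notable share of early-episode events where episodes are short. The article already warns that events may be few. A look-back rule also narrows the treated population to which the effect applies, and the report should say so.
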